### Information from medical records

Treatment outcomes that will be collected through medical record review for cases with extracapsular extension, seminal vesicle involvement or positive surgical margins (confirmed by pathology reports) are: referral to radiotherapy, taken from the surgeon’s notes (including dates of surgery and referral) or in the case where there was no referral that radiotherapy was discussed and the reason(s) for not referring to radiotherapy; uptake of radiotherapy or enrolment into the RAVES trial from the radiation oncology database; and time between surgery and commencement of radiotherapy. Individual case records will be reviewed for a minimum of six months after initial radical prostatectomy.

Data will be abstracted from medical records at hospitals, cancer centres and urologists’ private consulting rooms using previously established methods [33].

Hospital level factors will be collected from centrally held records including specialist cancer centre and size. Patient level factors will be collected from the medical and hospital records including: month and year of birth, comorbidities, stage of cancer, Gleason score, PSA level at diagnosis, country of birth and private health insurance status. Remoteness of residence and socio-economic status (SES) of the cases will be assigned using their postcode of residence and the ARIA [70] and SEIFA [71], respectively.

Hormone therapy, comorbidities, pre-diagnostic PSA levels, Gleason score, country of birth, and health insurance status are potential barriers to referral for radiotherapy.

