3. Opinion leaders (reinforcing factor): A key aspect of the intervention will be the use of Urologist Clinical Leaders in each hospital, identified by peers as being educationally influential, to engage the target group. Clinical Leaders will reinforce key messages, persuade peers to participate in the study and will model targeted referral behaviours and promote practice change [64]. Following the education session, Clinical Leaders will provide ongoing peer support and engage in discussions with colleagues to seek and provide feedback on practice and any continuing barriers to change. The Clinical Leaders are members of the ACI Urology Clinical Network and were recruited by the Network Co-Chair, an expert opinion leader who is influential due to his authority and status amongst his peers [65]. The introduction of key messages by a national opinion leader in the video presented at the education session provides an additional level of peer-to-peer influence.

4. Audit and feedback (reinforcing factor): Following commencement of the intervention, urologists will be provided with ongoing feedback reports detailing the number of patients referred to radiation oncology, at the individual, hospital and study level, obtained through data extraction from medical records. The feedback report will also include information on the number of patients at high risk who are discussed at MDT meetings. The initial feedback report will include baseline data. Feedback will be provided via email or SMS depending on the preferred method of communication of each participant. Aggregated quarterly feedback reports will additionally be presented verbally by the Clinical Leader at MDT meetings.

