### Outcomes

Primary outcomes are patient referral to radiation oncology for discussion of adjuvant radiotherapy in line with guideline recommended care or referral to the RAVES trial (see the ‘RAVES Trial’ subsection for details). Secondary outcomes include: an initial patient consultation with a radiation oncologist; enrolment in the RAVES trial; and commencement of radiotherapy.

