### Data collection—data extraction from patients’ medical records

Outcome data to assess changes in healthcare practice will be collected through data extraction from urologists’ and radiotherapy patients’ medical records by independent, trained research assistants who are blind to the date that the intervention was commenced at the hospital. Baseline data will be collected retrospectively for patients undergoing a radical prostatectomy during January 2013 to November 2013. Pilot testing of the medical record review tools and processes will allow us to train the research assistants and establish and test data collection procedures.

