### Data analysis

The primary analysis will be conducted at the individual patient level using a generalized estimating equations (GEE) approach to account for repeated outcome observations within clusters (urologists and MDTs). The dependent variable for this analysis will be referral to a radiation oncology service for adjuvant radiotherapy or enrolment into the RAVES trial (versus no referral) for each prostate cancer case. The exposure variable will be the intervention status (pre versus post) of the hospital at the time of the post-prostatectomy consultation. Other independent variables will be added to the model if they are shown to be independently associated with radiotherapy referral and/or their inclusion in the model changes the linear coefficient of the intervention effect by more than 20% in absolute value. Analysis to determine the extent to which changes in urologists’ knowledge, attitudes and beliefs (Phase II) mediated any changes in referral patterns will be assessed by including clinicians’ change scores in the GEEs.

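### The referral component of the primary outcome rests on the surgeon's notes, with no stated cross-check, while feedback after crossover may change how fully referrals are written down

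*Protocol article*

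**What the plan says.** All references are to the protocol article.

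- **Primary outcome.** Under Data analysis (Phase I), the dependent variable is "referral to a radiation oncology service for adjuvant radiotherapy or enrolment into the RAVES trial (versus no referral").
- **Sources.** The section Information from medical records names a source for each item. Referral and its date are listed as "referral to radiotherapy, taken from the surgeon"'s notes. By contrast, the same sentence takes "uptake of radiotherapy or enrolment into the RAVES trial from the radiation oncology database". Where there was no referral, abstractors record whether radiotherapy was discussed and the reasons for not referring. The section also says "Data will be abstracted from medical records at hospitals, cancer centres and urologists"' private rooms.
- **Intervention.** Under Physician-focused components, the audit-and-feedback item gives urologists reports "detailing the number of patients referred to radiation oncology, at the individual, hospital and study level, obtained through data extraction from medical records". These begin after the intervention starts at the hospital.
- **Baseline.** Under Data collection, baseline covers operations from January to November 2013 and is abstracted retrospectively.
- **Safeguards.** Abstractors are people "who are blind to the date that the intervention was commenced at the hospital". Staff training and evaluation adds a 10% blinded re-review for inter-rater reliability.
- **Secondary outcomes.** Under Outcomes, these are "an initial patient consultation with a radiation oncologist; enrolment in the RAVES trial; and commencement of radiotherapy".

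**The concern.** The authors of the source notes are the unblinded clinicians whom the intervention targets, and the intervention feeds back to each of them a count drawn from medical records. A urologist who already refers but does not always write it down can raise his count by writing it down. That incentive exists only after crossover. It is absent from the 2013 baseline and from hospitals still waiting for their step.

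The quantity analysed is recorded referral, which is true referral multiplied by the share of referrals that reach the notes. If that share differs by phase, the comparison mixes a change in practice with a change in documentation. The safeguards act at the wrong stage. Blinding prevents a biased reading of the notes, and re-review tests whether two readers agree. Two blinded readers will agree that an unwritten referral is absent.

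There is a concrete consequence for individual men. Outside RAVES, a man who was seen by radiation oncology but has no referral entry in his surgeon's notes would, under the stated source rule, count as not referred.

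**Working it through.** **1. The plan's own figure.** Sample size and statistical power claims at least 80% power for 15% to 35% and 20% to 40% (30% of men at high risk) and for 20% to 35% (50% at high risk), with ICC 0.09–0.15. The check used the Hussey–Hughes variance, nine hospitals split 2, 2, 2, 2, 1 over five steps, six periods, and an assumed two-sided alpha of 0.05. Men per hospital-period = 1,348 × share ÷ (9 × 5), which is 9.0 at 30% and 15.0 at 50%.

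| Target | ICC 0.09 | ICC 0.15 |
|---|---|---|
| 15% to 35% | 0.867 | 0.877 |
| 20% to 40% | 0.827 | 0.839 |
| 20% to 35% | 0.810 | 0.826 |

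The claim reproduces. Spreading the same men over all six periods (9 × 6 = 54 cells) gives 0.74–0.82. The power figure neither supports nor refutes the present point. It fixes the scale: target effects of 15 to 20 points.

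**2. Spurious gain with true referral unchanged.**

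Recorded rate = true rate × capture share, so spurious gain = true rate × (capture after − capture before).

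- True rate 15–20%: the protocol's expected level at trial start. It is stated there for administration of radiotherapy and used as the starting referral rate in the power statement.
- Capture before 70–90%, after 90–100%: assumptions, because the documents give none.

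| True rate | Capture | Recorded | Spurious gain |
|---|---|---|---|
| 15% or 20% | 90% → 90% | unchanged | 0 |
| 15% | 90% → 100% | 13.5% → 15.0% | 1.5 points |
| 20% | 90% → 100% | 18.0% → 20.0% | 2.0 points |
| 15% | 70% → 100% | 10.5% → 15.0% | 4.5 points |
| 20% | 70% → 100% | 14.0% → 20.0% | 6.0 points |

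The range is therefore 0 to 0.20 × 0.30 = 6 points.

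**3. What this does to the test.** The same variance formula was applied with 54 cells, a true rate of 20% throughout and 30% at high risk. The figures are the chance of a significant *increase*, to be compared with 2.5% (the upper half of a two-sided 5%).

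- Capture 80% → 95% (3 points): about 7%.
- Capture 70% → 95% (5 points): about 13%.

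**4. Could recording alone mimic the planned effect?** A spurious 20 points needs, for example, a true rate of 40% with capture rising from 50% to 100% (0.40 × 0.50 = 0.20). That is far outside the range in step 2.

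**The case against.** **Radiation oncology records are already used.** This is correct. RAVES enrolment is part of the primary outcome and comes from the radiation oncology database, and the article also names radiotherapy patients' records and cancer centres. A reader might infer that the whole primary outcome is read only from the surgeon's notes. The documents do not support that. The point is confined to the referral component.

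**A check exists.** Consultation and radiotherapy start are secondary outcomes. A pure recording artefact would raise noted referrals without raising these, so they would help to expose it. They do not correct the primary estimate, and they cannot confirm a referral that the man did not take up. The stated aim is referral for discussion, whether or not treatment follows.

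**Silent notes can be told apart from documented non-referral.** This is a fair point. Because discussion and reasons for not referring are collected, completeness of notes could be compared by phase. The article does not say that it will be, and the comparison would still not recover a missing referral.

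**The detail may sit in an abstraction manual.** Possibly so. The article cites established methods and piloted tools. But it does fix a source item by item, and for referral that source is the surgeon's notes.

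**The change in recording is inferred.** This stands. No capture rate is given, and the mechanism is plausible but not demonstrated.

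A reader might also infer an opposite bias, in which flagged cases are referred by the multidisciplinary team and never reach the surgeon's notes. The article says flagged cases go to the meeting for discussion, with the intent of increasing referral. It describes no route that bypasses the urologist, so no size is claimed for such a bias.

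**Conclusion.** The point holds for the referral component. Its source is the notes of the unblinded clinicians under study, no confirmation against radiation oncology records is stated, and individual feedback may improve recording in one phase only. Under the assumed capture rates and an unchanged true referral of 15–20%, the spurious gain is 0 to 6 percentage points. That can bias the estimate and raise the chance of a false positive result. It should not be read as able to produce the planned 15–20 point effect by itself. The size rests wholly on assumed capture rates, and at equal capture in both phases the spurious gain is zero. The change is worth making because it is specific and cheap, not because the design fails without it.

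**What to change.** State one rule, applied identically to baseline, control and intervention periods. A man counts as referred if either of these holds:

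- a dated referral is in the surgeon's notes; or
- the radiation oncology or cancer-centre records already abstracted show, within the same post-operative window, a post-prostatectomy consultation, radiotherapy start, RAVES enrolment or, where such entries are held, a referral received.

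Fix the window in advance and keep it the same for both phases. Report by phase how many referrals were captured by the notes only, by the radiation oncology side only, and by both. That table shows directly whether recording shifted.

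**Cost.** Slightly more abstraction and linkage, plus a few lines in the analysis plan. Consultation, radiotherapy start and RAVES enrolment are already collected. Whether radiation oncology records hold entries for men who never attended is not stated, so referral received can be used only where it exists. Referrals that are neither noted nor taken up may still be missed.

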### Study sample

The unit of study will be the participating multidisciplinary teams (MDT). Nine public hospital-based MDTs in NSW will participate. The hospitals are located in both metropolitan and regional areas. Approximately four to ten urologists will be included at each site.

### Data analysis

The primary analysis will be conducted at the individual patient level using a generalized estimating equations (GEE) approach to account for repeated outcome observations within clusters (urologists and MDTs). The dependent variable for this analysis will be referral to a radiation oncology service for adjuvant radiotherapy or enrolment into the RAVES trial (versus no referral) for each prostate cancer case. The exposure variable will be the intervention status (pre versus post) of the hospital at the time of the post-prostatectomy consultation. Other independent variables will be added to the model if they are shown to be independently associated with radiotherapy referral and/or their inclusion in the model changes the linear coefficient of the intervention effect by more than 20% in absolute value. Analysis to determine the extent to which changes in urologists’ knowledge, attitudes and beliefs (Phase II) mediated any changes in referral patterns will be assessed by including clinicians’ change scores in the GEEs.

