## Methods

### Phase I: intervention rollout and implementation trial

#### Hypotheses

Compared with pre-intervention, a larger proportion of post-operative radical prostatectomy patients who are at high risk of recurrence (have extracapsular extension, seminal vesicle involvement or positive surgical margins) treated in hospitals after implementation of the intervention will receive a referral to radiation oncology for consideration of adjuvant radiotherapy or referral to the RAVES trial [Radiotherapy Adjuvant Vs Early Salvage (Protocol Number: TROG.08.03); see the ‘RAVES Trial’ subsection for details].

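### The primary analysis counts RAVES enrolment where the declared primary outcome is RAVES referral, leaving men referred to RAVES but not enrolled without a defined outcome

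*Protocol article*

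**What the plan says.** The protocol article describes the RAVES part of the primary endpoint in two ways.

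- **Referral.** The Phase I hypothesis is that a larger proportion of high-risk men "will receive a referral to radiation oncology for consideration of adjuvant radiotherapy or referral to the RAVES trial". The Outcomes section agrees: "Primary outcomes are patient referral to radiation oncology for discussion of adjuvant radiotherapy in line with guideline recommended care or referral to the RAVES trial". The Methods/Design paragraph of the abstract also speaks of referral to a trial of adjuvant versus salvage radiotherapy.
- **Enrolment.** The Phase I Data analysis section gives the dependent variable of the primary GEE analysis as "referral to a radiation oncology service for adjuvant radiotherapy or enrolment into the RAVES trial (versus no referral) for each prostate cancer case".

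Outcomes treats enrolment as a separate and lesser event: "Secondary outcomes include: an initial patient consultation with a radiation oncologist; enrolment in the RAVES trial; and commencement of radiotherapy".

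The section on information from medical records names two relevant items. One is "referral to radiotherapy, taken from the surgeon’s notes (including dates of surgery and referral". The other is "uptake of radiotherapy or enrolment into the RAVES trial from the radiation oncology database". Referral to RAVES is not named there.

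**The concern.** The intervention aims to change what urologists do, and the Aims section frames success as referral so that the man can make an informed decision. A man who is referred to RAVES, hears the options and declines has received what the intervention sets out to deliver. Enrolment depends in addition on his choice and on his eligibility.

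If the analysis follows its own section literally, a declared secondary outcome replaces one limb of the primary. Two analysts, one working from Outcomes and the other from Data analysis, could code the same man differently. Unless the wording is settled beforehand, that choice could be made after results are known.

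**Working it through.** The point is settled by comparing texts. The arithmetic shows only what the size would depend on.

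**1. The definitions side by side**

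| Section | RAVES event | Status |
|---|---|---|
| Abstract, Methods/Design | referral | outcome data |
| Hypotheses | referral | primary hypothesis |
| Outcomes | referral | primary |
| Outcomes | enrolment | secondary |
| Information from medical records | enrolment | only RAVES item named |
| Data analysis | enrolment | part of primary dependent variable |

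No section says that referral and enrolment are treated as one event, or that every RAVES referral counts as a radiation oncology referral.

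**2. Which men are affected**

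| Man | Outcomes | Data analysis |
|---|---|---|
| Referred to radiation oncology | success | success |
| Referred to RAVES and enrols | success | success |
| Referred to RAVES, does not enrol, radiation oncology referral also recorded | success | success |
| Referred to RAVES, does not enrol, no radiation oncology referral recorded | success | unassigned |
| Not referred | failure | failure |

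Only the fourth row differs. That man meets neither success limb, yet he is not someone without a referral. He might be scored 0, scored 1 or dropped.

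**3. What the size would depend on**

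Let d0 and d1 be the shares of high-risk men in the fourth row in the control and intervention phases, and p0 and p1 the true success rates. If these men are scored 0:

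analysed difference = (p1 − d1) − (p0 − d0) = (p1 − p0) − (d1 − d0).

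The article gives neither d0 nor d1. If they are equal, both rates fall but the absolute difference does not change.

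**4. Illustration against the stated power**

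Inputs from Sample size and statistical power: 1,348 prostatectomies, nine clusters, six intervals, ICC 0.09 to 0.15 and at least 80% power for three scenarios. High-risk men: 1,348 × 0.30 = 404 and 1,348 × 0.50 = 674 (the article prints 671; the difference does not matter here).

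Assumptions not in the article: two-sided alpha 0.05; hospitals crossing over 2, 2, 2, 2, 1; men spread evenly over 9 × 5 = 45 hospital-blocks (404/45 ≈ 9.0 and 674/45 ≈ 15.0 per cell), with the same cell size at baseline.

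Method: Hussey-Hughes model with fixed period effects. With σ² the mean of p0(1 − p0) and p1(1 − p1), ICC ρ and cell size m, each hospital's cell means have covariance V = [(1 − ρ)σ²/m]I + ρσ²J. Var is the treatment entry of the inverse of ΣZ′V⁻¹Z, and power = Φ(|p1 − p0|/√Var − 1.96).

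The first results column reproduces the plan's claim. The others assume that a share r of true successes is scored 0 in both phases, so each rate becomes p(1 − r). Ranges run over ICC 0.09 to 0.15.

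| Scenario | r = 0 | r = 10% | r = 20% |
|---|---|---|---|
| 15% to 35%, 30% high risk | 88.5–89.4% | 83.6–84.7% (13.5% to 31.5%) | 77.5–78.8% (12% to 28%) |
| 20% to 40%, 30% high risk | 84.5–85.6% | 78.7–79.9% (18% to 36%) | 71.8–73.2% (16% to 32%) |
| 20% to 35%, 50% high risk | 82.1–83.7% | 76.3–78.0% (18% to 31.5%) | 69.6–71.5% (16% to 28%) |

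The stated power is reproduced on this reading. If the same men are spread over all six intervals it is 75% to 84%, but the article has a separate baseline period, so the five-block reading is the natural one. The values of r are invented for illustration.

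**The case against.** The best defence is that few men, perhaps none, fall in the disputed row. RAVES compares two timings of radiotherapy, and enrolment is read from the radiation oncology database. The power statement concerns referral to a radiation oncologist with no separate RAVES limb, and the feedback reports count radiation oncology referrals. All this suggests that a RAVES referral would usually go through radiation oncology and satisfy the first limb. The analysis section's contrast with no referral also fits loose drafting of a referral outcome at least as well as a deliberate enrolment endpoint. This stands as a limit on size, but it does not remove the conflict, because no section states the overlap.

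The extraction form is not shown and an article condenses it. Referral and its date already come from the surgeon's notes, with reasons where no referral was made, so RAVES referral may well be recoverable. This too stands: the article does not establish that the form lacks the item.

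Four stronger readings are tempting and are not supported:

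- **That these men are definitely scored as failures.** The text leaves them unassigned.
- **That 1.5 to 7 percentage points of the 15 to 20 point target are lost.** One could assume that 5–10% of high-risk men are referred through RAVES and 30–70% of those enrol, giving 0.05 × (1 − 0.70) = 1.5 points to 0.10 × (1 − 0.30) = 7 points. Both inputs are guesses. The result is a level of misclassified men, whereas the target is a difference between phases.
- **That the loss falls mainly in the intervention phase.** The text on the intervention components nowhere mentions encouraging RAVES referral.
- **That omitting the word discussion from the analysis section narrows the outcome.** The article varies this phrase elsewhere, and no different set of patients is shown. It reads as condensed wording.

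**Conclusion.** The conflict is real, lies in current text and concerns the primary endpoint. Data analysis uses RAVES enrolment where the abstract, Hypotheses and Outcomes use RAVES referral, and Outcomes makes enrolment secondary. The outcome of a man referred to RAVES who does not enrol is therefore undefined in the primary analysis unless a radiation oncology referral is also on record.

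The likely direction is under-counting of successes. An enrolled man would ordinarily have been referred first, so counting enrolment should add few or no false successes; this is a reasonable inference, not something the article states. The size cannot be computed from the article and may be small. The power figures above show sensitivity under assumed losses and do not estimate an effect on this trial. The contradiction depends on none of them.

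**What to change.** In the Phase I Data analysis section, define the dependent variable as in Outcomes: referral to radiation oncology for discussion of adjuvant radiotherapy, or referral to RAVES whether or not the man enrols, against neither referral. Keep RAVES enrolment as a secondary outcome only. Make sure that RAVES referral and its date are among the items taken from the surgeon's notes.

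The cost is one sentence and, if the form does not already hold it, one field from notes already being read. The Figure 3 legend puts the end of data collection at September 2015, after the December 2013 start, so the field can be added during collection. The design, sample size and stated power are unchanged.
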